### **Rationale**

AF treatment guidelines are largely informed by randomised controlled trial (RCT) results, but we do not know if these findings apply to large patient populations not studied in trials. Apixaban is one of the most widely used anticoagulants used in stroke prevention in AF. It was studied in a large randomised trial (ARISTOTLE), but we don't know the effects of treatment in important patient groups who were not studied. Some were excluded from AF stroke prevention trials in general (e.g. those with mechanical heart valves and those with substantial comorbidity) and some are under-represented (e.g. elderly patients), meaning conclusions about these groups are difficult to make. The results we generate will firstly tell us if EHR data are suitable for this purpose. If so, our findings will aid patients, prescribers and policy makers in better understanding the benefits and risks of different anticoagulants for stroke prophylaxis in AF rather than assuming that the trial estimates are applicable to all patients.

[figure not shown]

## F. Study Background

Atrial fibrillation (AF) is a heart condition in which the patient experiences a rapid and irregular heartbeat caused by electrical signals firing from multiple locations in the atria. Although patients may be asymptomatic, symptoms such as heart palpitations, fainting, light-headedness, and shortness of breath are reported. The prevalence of AF is estimated to be around 3% and increases with age from 0.2% in people aged 45-54 years to 8.0% in those 75 and older. The lack of organised atrial contraction in AF can lead to blood stagnating in the left atrium or left atrial appendage and the formation of thrombi. Should a thrombus move from the heart through the body this can cause systemic embolism or stroke; consequently patients with AF have a five fold higher risk of stroke. It is recommended that AF patients receive prophylactic treatment with anticoagulation medication to reduce the risk of stroke. The previous standard anticoagulation treatment for this indication, warfarin, has many treatment interactions and requires frequent monitoring and dose adjustments to stay within the therapeutic range of anticoagulant action as summarised by Hirsh et al: Warfarin has interactions with a wide range of drugs such as metronidazole which inhibits warfarin clearance, barbiturates and carbamazepine which increase hepatic warfarin, and aspirin which increases the risk of bleeding. Diet also interacts with response to warfarin with increased intake of vitamin K (present in green vegetables) leading to a reduction in the anticoagulant response to warfarin. Genetics influences the warfarin dose-response relationship most notably in common mutations in coding for cytochrome P450 (the family of enzymes responsible for warfarin metabolism). Warfarin therapy is monitored by calculating a patient's International Normalised Ratio (INR), a standardised measurement of the time taken for blood to clot. Typically for AF the patient must maintain INR at a therapeutic range between 2.0 and 3.0 with INR values below 2 putting a patient at higher risk of stroke and levels above 3 resulting in a higher risk of bleeding. On initiation of therapy INR is checked daily until in therapeutic range, then 3 times weekly for 2 weeks, then less often, according to the stability of the results. Given the challenge in maintaining INR in therapeutic range and the complex safety profile of warfarin it was hoped that the introduction of the direct acting oral anticoagulants (DOACs) would provide a safer and easier to manage long term anticoagulation therapy for AF patients. The pivotal trial of the DOAC apixaban for this indication, ARISTOTLE, demonstrated superiority over warfarin for both the primary efficacy (prevention of stroke) and safety (major bleeding) outcomes.

Apixaban was licensed based on the results of the pivotal trial ARISTOTLE, a randomised controlled trial (RCT). ARISTOTLE had eligibility criteria that patients had to meet to be included in the trial, thus limiting the generalisability of the results of the trial. As a result, evidence on treatment effect is lacking for patients who would not have met the ARISTOTLE eligibility criteria such as individuals with a mechanical heart valve, those at increased bleeding risk, and individuals with severe comorbid conditions. The regulatory environment now demands evidence of treatment effectiveness outside the confines of randomised trials. Non-interventional data sources have the potential to overcome many of the RCT limitations given that they contain data for a wide spectrum of patients treated with the drug in routine care including patients who would have been excluded from trials. Data collected as a standard part of patient care such as electronic healthcare record (EHRs) provide a valuable opportunity to obtain evidence on the effectiveness of apixaban in a routine care setting. A key problem with non-interventional studies using these data is that the absence of randomisation leaves them highly susceptible to confounding (with confounding by indication a particular problem), making it difficult to have confidence in the results. By contrast matching to individual patient data from ARISTOTLE and then using novel methods for matching within EHR treatment groups should result in an EHR population similar to the trial population that is well balanced by treatment group. If successful, the estimates of effectiveness and safety of apixaban obtained from this approach should then be comparable with the ARISTOTLE results. If non-interventional data can be successfully used to approximate the findings of ARISTOTLE then they may be reliable to estimate effects in under studied AF patient groups. This project will involve testing whether EHR data can find results compatible with the ARISTOTLE trial results while developing optimal methodology for studying anticoagulants in stroke prophylaxis. This methodology can then be applied to under studied AF patient groups.

## G. Study Type

Hypothesis testing

## H. Study Design

This is a historical cohort study.

The cohort study design allows measurement of the effects of prescribing apixaban vs warfarin for prevention of stroke and systemic embolism in AF on key efficacy and safety outcomes..

[figure not shown]

**I. Feasibility counts**

ARISTOTLE inclusion and exclusion criteria were extracted from the trial protocol. Read code and medication codelists were created for the inclusion and exclusion criteria. The criteria were applied to a January 2018 extract of CPRD Gold patients prescribed apixaban. Overall out of 13 332 patients with a prescription for apixaban and diagnosis of AF 63% (8 407) were trial-eligible. Trial criteria were also applied to patients with a prescription for warfarin in the period 01 January 2013 to 31 January 2018 and a diagnosis of AF (68 113 patients). Of these patients 45 435 (62.3%) were eligible according to trial criteria.

**J. Sample size considerations**

We will include all eligible patients registered in the CPRD and who meet the trial criteria. In ARISTOTLE there were 9120 subjects in the apixaban arm therefore it was estimated a minimum of 15,000 EHR patients exposed to apixaban were needed for matching to be feasible. It was unlikely there would be enough patients in CPRD Gold alone for the project given that only ~8400 patients were eligible in the January 2018 extract. The CPRD Aurum database (June 2019 extract) contained 29,578 patients with both an atrial fibrillation diagnosis and a prescription for apixaban; of these patients 23,526 were not registered in practices that had previously contributed data to CPRD Gold. Using the assumption that the proportion of Aurum patients who would meet the ARISTOTLE trial eligibility criteria would be similar to the proportion of Gold patients (~60%) gave an estimate of 14,115 trial eligible Aurum patients in the apixaban arm. Combining the Gold and Aurum cohorts is therefore estimated to give >22,000 unique trial-eligible EHR apixaban patients.

**K. Planned use of linked data (if applicable):**

We intend to use CPRD data linked with HES in patient data to enable optimal stroke, MI, and major bleeding ascertainment, and ONS mortality data to determine deaths. When matching CPRD patients we plan to include the practice level deprivation level index as a matching variable because socioeconomic status is predicted to influence the likelihood of the primary study outcome of stroke.

[figure not shown]

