- no severe comorbid condition with life expectancy of  $\leq 1$  year,
- no active alcohol or drug abuse, or significant psychosocial difficulties (e.g., psychosis, dementia),
- no recent ischemic stroke (within 7 days),
- no severe renal insufficiency (serum creatinine > 2.5 mg/dL or a calculated creatinine clearance < 25 mL/min),
- no ALT or AST > 2X ULN or a Total Bilirubin  $\geq 1.5$ X ULN (unless an alternative causative factor such as Gilbert's syndrome is identified),
- no platelet count  $\leq 100,000/\text{mm}^3$ ,
- no haemoglobin < 9 g/dL,
- no prior exposure to apixaban,
- no women who are pregnant or breastfeeding

For the 3 criteria involving patient laboratory results (renal insufficiency, low platelet count, and low haemoglobin) a patient will be excluded if their last test result in the 90 days prior to the index date meets the exclusion criteria.

**Step 2:** Next we will determine if/when these patients received apixaban or warfarin. Individuals in EHR who have more than one warfarin eligibility period within their record will be able to contribute more than once to the pool of warfarin subjects (with the covariates and person-time contributed unique to the specific eligibility period) as long as they have no past apixaban exposure.

**Step 3:** Having obtained individual level patient data for ARISTOTLE participants from Bristol Myers-Squibb we will then match each ARISTOTLE apixaban participant 1:1 with the closest available apixaban patient record in our EHR pool. We will consider matching on a selection of the following ARISTOTLE baseline characteristics:

- age
- sex
- body mass index
- systolic blood pressure (mmHg)
- history of congestive heart failure or left ventricular systolic dysfunction

[figure not shown]

- hypertension requiring pharmacological treatment
- diabetes mellitus
- prior stroke or TIA or thromboembolism
- smoking status [current smoker, former smoker, or never smoked]
- alcohol consumption [none, low, moderate, heavy]
- renal impairment [severe, moderate, mild, normal based on the CrCL value]
- prior VKA/warfarin use
- concomitant treatment with:
  - anticoagulant/VKA use other than warfarin or apixaban
  - aspirin
  - antiplatelets
  - NSAIDs
  - lipid lowering drug therapy
  - CYP3A4 inhibitors

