## **O. Data/ Statistical Analysis**

### **Data mapping**

For all 3 objectives the data source will consist of two datasets of UK real world clinical data which will be combined: CPRD Gold and CPRD Aurum. The two datasets will be mapped to a common data model based on adapted Clinical Data Interchange Standards Consortium (CDSIC) standards. Duplicate entries of patients – where a patient is present in more than one dataset – will be removed with the following rule: keep in CPRD Aurum above CPRD Gold. CPRD Aurum provides a dataset listing practices in CPRD Aurum which have previously contributed data to CPRD Gold; this dataset will be used to exclude data from practices with eligible patients in CPRD Gold where the patient data is also recorded in Aurum. Only data of interest to the study will be mapped and used: patient demographics, diagnoses, clinical events, and recorded symptoms, therapies prescribed, lab results, and vital signs.

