##### **Missing Prescription Data**

Treatment may be initiated in secondary care meaning the first prescription of patients newly initiating treatment is missing. To account for these potentially missing first prescriptions we will perform a sensitivity analysis where those newly initiating treatment are assumed to have a missing earlier prescription and therefore assigned an earlier derived index date. Patients who are hospitalised may also have prescriptions issued in secondary care leading to treatment gaps seen in their primary care prescription data. The primary analysis using the Prescribed Population will not be affected by such gaps as patient time is included until the patient is censored or experiences an event regardless of treatment gaps. The supplementary analysis using the On-treatment Population and the safety analysis censor at derived date of last dose and may therefore miss events whilst a patient was on treatment in hospital. We will investigate the occurrence of hospitalisation around treatment discontinuation and assess the potential impact on the results of such missed events by performing a sensitivity analysis with different extended derived dates of last dose (extending the final period to 60 or 90 days after the final prescription estimated end).

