##### **Missing Outcome Data**

The problem of missing data on the outcome events will be addressed by performing a sensitivity analysis repeating the primary analysis on the ONS and HES-linked cohort. The linked cohort will be assembled by restricting the trial-eligible cohort to the patients with ONS-linked and HES-linked data prior to matching. Occurrence of events and detail of events (such as type of stroke) is expected to be better recorded in the linked cohort.

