#### **T. Limitations of the study design, data sources, and analytic methods**

Some of the criteria that should be assessed for ARISTOTLE eligibility may not be well recorded in CPRD. Criteria such as “increased bleeding risk” are vague and it is not clear exactly which Read codes should be included and time scale considered. Other criteria such as alcohol and drug abuse may not be captured for all patients in CPRD. These limitations are consistent with our aim to select a population as similar as possible to the ARISTOTLE trial population with the acknowledgment that differences will remain. The most important risk factors for the primary outcome of stroke (the components of the CHA2DS2-VASc score for AF stroke risk of age, sex, history of congestive heart failure, hypertension, stroke/TIA history, vascular disease history, and diabetes) are mostly well recorded in CPRD.

There are differences in the coding systems used by the two datasets and it is possible that the completeness of coding differs between the two. The potential impact of the different coding systems and completeness of coding will be ascertained by comparisons of the rates of diagnoses, events, baseline variables (such as smoking status, alcohol use, lab values, and vital signs), and prescriptions of interest. Including the data source (Gold or Aurum) as one of the matching variables should prevent discrepancy between the two datasets from biasing the results.

The main focus of the study is the validation of our methodology through assembling a cohort of patients comparable to the patients included in ARISTOTLE and finding similar results to the trial. Criteria to determine the success of the methodology have been pre-specified in the protocol. Given the use of CPRD data to determine treatment effectiveness is not yet well established, a finding that these data are not suitable to answer questions on intended effectiveness will be a useful conclusion.

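### Section K gives hospital data a role in outcomes only, omits systemic embolism, and no section uses them for exclusions or baseline histories, although HES is already requested

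*Protocol*

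**What the plan says.** Section K assigns the linked data: "We intend to use CPRD data linked with HES in patient data to enable optimal stroke, MI, and major bleeding ascertainment". Mortality is to come from the ONS link. Systemic embolism is not in that list, although section O makes stroke or systemic embolism the primary efficacy endpoint.

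On eligibility, section I reports that "Read code and medication codelists were created for the inclusion and exclusion criteria". The only code list in the appendices, for atrial fibrillation, is a Read list. Section O (Data mapping) names CPRD Gold and CPRD Aurum as the data source for all three objectives. Section T concedes that "Some of the criteria that should be assessed for ARISTOTLE eligibility may not be well recorded in CPRD" and discusses the difficulty in terms of Read codes.

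Section L, Objective 1, Step 1 selects patients described as HES and ONS linked. It then lists exclusions such as "no recent ischemic stroke (within 7 days"), previous intracranial haemorrhage (given as an example of bleeding risk) and active infective endocarditis. Heart failure and prior stroke or embolism are stroke risk factors in Step 1 and candidate matching variables in Step 3.

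Section Q (Missing Prescription Data) accepts that "Treatment may be initiated in secondary care meaning the first prescription of patients newly initiating treatment is missing". Section Q (Missing Outcome Data) makes the linked cohort a sensitivity analysis, on the ground that "Occurrence of events and detail of events (such as type of stroke) is expected to be better recorded in the linked cohort".

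**The concern.** Several exclusions and matching variables are conditions that are typically diagnosed or treated in hospital. If they are read from GP records alone, a diagnosis made shortly before the index date may not yet be in the record. The 7-day stroke exclusion is the most exposed, because it depends on information that is at most a week old.

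Two things are at stake. First, patients whom the trial would have excluded could enter the ARISTOTLE-analogous cohort, and histories used for matching could be misclassified. This can happen whether or not the arms differ. Second, if recording is less complete in one arm, matching on recorded history leaves an imbalance in true history. The hazard ratio that decides the validation in section O would then carry a bias.

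The omission of systemic embolism is separate and needs no assumption about bias. Section N treats the absence of a record as the absence of the event, so an embolism known only to the hospital would count as no event.

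**Working it through.** The protocol states no figure on this point, so there is nothing to reproduce. The check is a comparison of passages, followed by a calculation for scale.

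**Passages side by side**

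- *HES for outcomes:* section K names stroke, MI and major bleeding. Systemic embolism is absent there but present in the primary endpoint in section O.
- *HES for baseline:* no section mentions it. Section N takes baseline values at or before first dose without naming a source. Sections I and T and the appendix speak of Read codes or CPRD recording.
- *Availability:* HES Admitted Patient Care is ticked in item 13, and Step 1 in section L selects linked patients.
- *Hospital initiation:* section Q answers it with a sensitivity analysis that moves the index date earlier. This addresses the prescription only. It also leaves less time for a diagnosis to reach the GP record before index.
- *Linked or not:* section L, Step 1 reads as if every Objective 1 patient is linked. Section Q forms the linked cohort by restricting the trial-eligible cohort, and only for a sensitivity analysis. Both cannot describe the primary cohort.

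**Size if completeness differs by arm**

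Every input is an assumption; the documents give none of them. Let p be the true prevalence of a history such as prior stroke (equal in both arms, no false positives), s the share recorded at index, and h the hazard ratio for that history.

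True history among patients with none recorded: u = p(1 − s)/(1 − ps).

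After exact matching on recorded history, with the recorded share r = p × s(apixaban) in both arms, the mean relative hazard in an arm is r·h + (1 − r)(1 + u(h − 1)). The bias factor is this quantity for apixaban divided by that for warfarin.

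Worked case, p = 0.20, h = 2, s = 0.7 (apixaban) and 0.9 (warfarin):

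- u(apixaban) = 0.06/0.86 = 0.0698
- u(warfarin) = 0.02/0.82 = 0.0244
- r = 0.14
- apixaban: 0.28 + 0.86 × 1.0698 = 1.200
- warfarin: 0.28 + 0.86 × 1.0244 = 1.161
- factor = 1.200/1.161 = 1.034

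| p | h | s, apixaban | s, warfarin | Factor |
|---|---|---|---|---|
| any | any | 0.8 | 0.8 | 1.000 |
| 0.15 | 2 | 0.8 | 0.9 | 1.013 |
| 0.20 | 2 | 0.7 | 0.9 | 1.034 |
| 0.25 | 2.5 | 0.6 | 0.9 | 1.086 |
| 0.20 | 2 | 0.9 | 0.7 (gap reversed) | 0.970 |

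Over p 0.15-0.25, s 0.6-0.8 (apixaban) and 0.8-0.9 (warfarin), and h 2-2.5, the factor runs from 1.000 to 1.086. A wider set with the gap reversed (p 0.10-0.30, h 2-3, s 0.95 for apixaban and 0.80 for warfarin) gives 0.951 to 0.987.

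**Against the validation window**

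At the largest factor, 0.79 × 1.086 = 0.858, inside 0.69 to 0.99. An upward bias of that size would carry the estimate past 0.99 only if the unbiased HR were above 0.99/1.086 = 0.912.

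**The case against.** The strongest reply is that much of this is inference from silence. Section K says what HES is intended to enable; it does not rule out a baseline use. Step 1 names linkage at the eligibility step itself, and the Read lists in section I belong to a feasibility count on one CPRD Gold extract. The source behind each code list is often left to a later document. This stands in part: the protocol does not forbid HES at baseline. But section K is the place where linked-data use is declared, and followed as written it leaves baseline and systemic embolism to GP records.

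A reader might go further and infer that GP coding is known to lag in hospital-started patients, that the two arms are recorded to different completeness, and that the HR is therefore pushed upward. The documents do not support this:

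- They give no coding delay, no rate of hospital initiation and no completeness by arm.
- Section Q regards important comorbidity as well recorded, and section T says the main stroke risk factors are mostly well recorded. Neither addresses timing around a hospital start.
- Prior warfarin or VKA use is a candidate matching variable (section L) and a covariate in the Cox model (section O), which narrows any contrast between recent starters and established users.
- Warfarin may also be started in hospital, and some apixaban patients come from warfarin with long records.
- Where the first prescription was issued in hospital, the GP-based index date falls later, which gives more time for coding.

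An asymmetry remains possible, because section O compares starting apixaban with starting or continuing warfarin. Its direction is unknown, and the assumed ranges include no bias at all.

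**Conclusion.** The point holds as a gap in the stated use of data, with a cheap and better method at hand. Three parts rest on the text alone: systemic embolism is missing from the HES-ascertained outcomes; no section gives HES a role in exclusions or baseline histories; and hospital initiation is remedied only for prescriptions. It follows that hospital-type diagnoses may be missed at index, with trial-ineligible patients admitted and matching variables misclassified. How often this would happen cannot be read from the protocol.

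Bias in the hazard ratio is conditional on completeness differing by arm, and may go either way. On the assumed inputs the factor is 1.00 to about 1.09, and below 1 if the gap is reversed. From 0.79 this stays inside the validation window; an HR already near a limit could be moved across it. The change is worth making before the cohort is built, but the calculation does not show that the planned result will be wrong.

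**What to change.** Amend section K in four respects.

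1. For linked patients, use HES admissions dated before the index date together with CPRD for the hospital-type exclusions in Step 1 and the history variables in Steps 3 and 4.
2. Add systemic embolism to the outcomes ascertained through HES.
3. Report baseline histories by arm with and without HES, and keep a CPRD-only baseline as a sensitivity analysis. The comparison by arm would show whether completeness differs and in which direction. HES removes the bias only so far as it equalises recording between the arms.
4. Reconcile section L, Step 1 (linked patients selected) with section Q, Missing Outcome Data (linked cohort only as a sensitivity analysis), since the first three changes depend on which patients are linked.

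The cost is a set of ICD-10 code lists for a few conditions and a change of wording. No new data are needed. Some patients will become ineligible, so the eligible pool will be slightly smaller.

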##### Area Level Data (place 'X' in all boxes that apply)

| Practice level (UK)                                                                    |   | Patient level (England only)                |   |
|----------------------------------------------------------------------------------------|---|---------------------------------------------|---|
| Practice Level Index of Multiple Deprivation (Standard)                                | X | Patient Level Index of Multiple Deprivation | X |
| Practice Level Index of Multiple Deprivation (Non-standard)                            |   | Patient Level Townsend Score                |   |
| Practice Level Index of Multiple Deprivation Domains (Non-standard)                    |   |                                             |   |
| Practice Level Carstairs Index for 2011 Census (Excluding Northern Ireland) (Standard) |   |                                             |   |
| 2011 Rural-Urban Classification at LSOA level (Non-standard)                           |   |                                             |   |

[figure not shown]

Reference number (where applicable):

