## L. Definition of the Study population

For all objectives two datasets of UK primary care data will be combined: CPRD Gold and CPRD Aurum. Patients with a prescription for an oral anticoagulant in the time period 01 January 2013 to 31 January 2019 (exact cut-off date dependent on date of final data extracts) and a prior diagnosis of atrial fibrillation will be selected as the EHR cohort. Apixaban gained UK marketing authorisation in January 2013 for the indication of prevention of stroke and systemic embolism in AF patients; the minimum date is set to capture all patients prescribed apixaban for this indication in the UK. A previous study validated the use of diagnostic read codes for identifying patients with AF in CPRD by sending surveys to GPs and found a confirmation rate of 98% among patients originally identified with AF codes.

### Objective 1

**Step 1:** We will select all (HES and ONS linked) patients in the EHR cohort who would have met the following eligibility criteria for inclusion in the ARISTOTLE study, at least 6 months after patient registration in an up to standard practice: or 6 months post-UTS date, whichever is later:

- a diagnosis of AF,
- age over 18 years,
- at least one of the following risk factors for stroke: diagnosis of congestive heart failure, hypertension requiring pharmacological treatment, age greater than 75, diabetes mellitus, and prior stroke or systemic embolism,
- no AF due to reversible causes (e.g. thyrotoxicosis, pericarditis),
- no clinically significant (moderate or severe) mitral stenosis, in EHRs clinical significance and severity are not consistently recorded therefore a diagnosis of mitral stenosis will be sufficient to exclude a patient,
- no increased bleeding risk that is believed to be a contraindication to oral anticoagulation (e.g. previous intracranial haemorrhage),
- no conditions other than AF that require chronic anticoagulation (e.g. prosthetic mechanical heart valve),
- no persistent, uncontrolled hypertension (systolic BP > 180 mm Hg, or diastolic BP > 100 mm Hg), in EHRs this will be implemented by excluding patients whose latest blood pressure reading in the 6 months prior to the index date is over the systolic or diastolic blood pressure limit
- no active infective endocarditis,
- no concomitant treatment with aspirin > 165 mg/day,
- no simultaneous treatment with both aspirin and a thienopyridine (e.g., clopidogrel, ticlopidine),

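### Section K matches on practice-level deprivation and gives the requested patient-level index no role; the better choice depends on whether the primary cohort is linked-only, which the protocol leaves unresolved

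*Protocol*

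**What the plan says.** Section K, on the planned use of linked data, is the only place where the protocol states how deprivation will be measured for matching: "we plan to include the practice level deprivation level index as a matching variable". The reason given is "because socioeconomic status is predicted to influence the likelihood of the primary study outcome of stroke".

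Section 13 (Area Level Data) marks two deprivation measures. One is the standard practice-level IMD, in a column covering the UK. The other is the "Patient Level Index of Multiple Deprivation", in a column limited to England. No later section gives the second measure a use.

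Deprivation is not among the trial baseline characteristics listed in Section L, Step 3, so it enters at Step 4, the match between treatment arms. There, and again in Section N, socioeconomic status is listed for consideration without a level.

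On who forms the cohort, Section L, Step 1 states: "We will select all (HES and ONS linked) patients in the EHR cohort". Section Q (Missing Outcome Data) instead proposes "performing a sensitivity analysis repeating the primary analysis on the ONS and HES-linked cohort", obtained by restricting the trial-eligible cohort before matching.

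**The concern.** The protocol treats socioeconomic status as a predictor of the primary outcome and therefore as a potential confounder of the apixaban-warfarin comparison. It then plans to control it with a score that does not vary within a practice. Two patients of one practice, one from a deprived neighbourhood and one not, count as perfectly matched on deprivation. The same holds for patients of different practices that share a score. If the newer drug went preferentially to better-off or worse-off patients within practices, the match would not remove that difference. A finer measure has already been requested and is left without a purpose.

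What is at stake is the Objective 1 hazard ratio. Section O judges agreement with ARISTOTLE partly by whether the point estimate lies between 0.69 and 0.99, and Objectives 2 and 3 reuse the method. A small shift matters most near the upper edge of that window.

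**Working it through.** **1. Which measure covers whom.**

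| Place | What it implies |
|---|---|
| Section 13 | Practice-level IMD covers the UK; patient-level IMD covers England only; both are requested |
| Section K | Practice-level index named for matching |
| Section L, Step 4; Section N | Socioeconomic status to be considered, level not given |
| Section L, Step 1 | Eligible cohort is HES- and ONS-linked |
| Section Q, Missing Outcome Data | Linked cohort is a subset, used for a sensitivity analysis |
| Section J | All eligible CPRD patients, no linkage restriction stated |

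The Section J estimate can be reproduced: 23,526 × 0.60 = 14,115.6 (stated as 14,115), and 8,407 + 14,115.6 = 22,522.6 (stated as more than 22,000). Neither step reduces the count for linkage, so the sizing agrees with Section Q rather than with Step 1.

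Two readings follow. If Step 1 governs, the primary cohort is linked, and patient-level IMD should be widely available in it. That availability is an assumption, because the documents do not state how complete the index is among HES- and ONS-linked patients. If Section Q governs, the primary cohort may contain patients without a patient-level value. The practice-level index is then the only requested deprivation measure that could cover everyone. On neither reading is patient-level IMD given a role.

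**2. What practice-level matching can balance.** Patient deprivation splits into a part explained by the practice score and a part that varies among patients with the same score. Matching on the practice score balances the first part only. The second part biases the hazard ratio only if it differs between arms and affects stroke after allowing for the other matched variables.

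**3. Possible size.** The documents give no deprivation distribution, no deprivation-stroke association and no imbalance between arms, so all inputs here are assumptions: 20% of patients deprived on average; deprivation-stroke hazard ratio h of 1.1, 1.3 or 1.5; difference d between arms, left after matching, of 2, 5 or 10 percentage points, with the apixaban arm less deprived.

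With p1 = 0.20 − d/2 (apixaban) and p0 = 0.20 + d/2 (warfarin), the approximate bias factor is [1 + p1(h − 1)] / [1 + p0(h − 1)].

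- Smallest case, h = 1.1 and d = 0.02: (1 + 0.19 × 0.1) / (1 + 0.21 × 0.1) = 1.019 / 1.021 = 0.998.
- Largest case, h = 1.5 and d = 0.10: (1 + 0.15 × 0.5) / (1 + 0.25 × 0.5) = 1.075 / 1.125 = 0.956.

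| h | d = 0.02 | d = 0.05 | d = 0.10 |
|---|---|---|---|
| 1.1 | 0.998 | 0.995 | 0.990 |
| 1.3 | 0.994 | 0.986 | 0.972 |
| 1.5 | 0.991 | 0.978 | 0.956 |

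Multiplied by 0.79, the extremes give 0.788 and 0.755. If the apixaban arm were the more deprived one, the largest case would invert: 1.125 / 1.075 = 1.047, and 0.79 × 1.047 = 0.827.

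**4. Effect on the agreement window.** A true hazard ratio of 1.00 would appear as 0.956 in the largest case and so fall inside 0.69 to 0.99. In the smallest case it would appear as 0.998 and stay outside.

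**The case against.** The strongest defence is that the practice-level index may be the right choice for the cohort actually analysed. The cohort is drawn from UK data, the sizing has no linkage restriction, Section Q makes the linked cohort a sensitivity analysis, and patient-level IMD exists for England only. On that reading the practice-level index is the one measure with common coverage. This stands, and it is why the recommendation has to be conditional. A reader of Step 1 alone might infer that linked patients certainly form the primary cohort and that the residual confounding is therefore simply avoidable. Sections J and Q do not support that as settled.

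It can also be said that Step 4 and Section N leave the level of socioeconomic status open, that Section L makes the final choice of variables depend on data quality and completeness, and that covariate definitions are commonly left to an analysis plan. This is fair, and patient-level IMD is not excluded. But Section K is the only text that names a level, and a programmer following the protocol would use it.

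A further defence is that other candidate matching variables (smoking, alcohol, BMI, blood pressure, diabetes, comorbidities) plausibly carry part of any deprivation effect, and that patient-level IMD is itself listed as area-level data and would not remove all socioeconomic confounding. Both points stand and limit the likely gain.

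Finally, a reader might connect this to the channelling discussed in Section P. That section raises channelling because apixaban was newly available; it mentions neither deprivation nor prescribing within practices, so it is not evidence that such an imbalance exists.

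**Conclusion.** The point holds in a limited form. The only deprivation measure assigned to matching is constant within a practice, and a finer one is requested but given no role. Practice-level matching cannot balance deprivation between arms within a practice.

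The resulting bias is unquantified. On the assumed inputs it runs from negligible (factor 0.998) to modest (factor 0.956), and its direction depends on which arm is more deprived. It would be tempting to express the size as the share of patient-level deprivation variance that the practice score leaves unexplained. The documents give no such share, and unmatched variance in a covariate is not bias in a hazard ratio. Material confounding is therefore not demonstrated.

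This does not threaten the validity of the study. It is an inexpensive improvement in the control of a factor that the protocol itself links to the primary outcome, and its form depends on resolving the cohort definition.

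**What to change.** First, reconcile Section L, Step 1 with Section Q (Missing Outcome Data) on whether the primary cohort is restricted to HES- and ONS-linked patients. Then state the deprivation measure in Sections K, L (Step 4) and N:

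- **If the primary cohort is linked-only:** use patient-level IMD, for example in quintiles, in the Step 4 between-arm match or propensity score. Use practice-level IMD only where the patient-level value is missing.
- **If it is not:** keep practice-level IMD for the full cohort and use patient-level IMD in the linked-cohort sensitivity analysis. This avoids one matching variable whose meaning changes with linkage status.

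The cost is small: a text change, a rule for missing patient-level values, and possibly slightly fewer matches. Both measures are already requested, so no new data application is needed.
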